### ARDS and positioning

Different techniques exist for positioning patients with ARDS

In 2005, Hoste et al. (HOSTE; Intensive Care Med; 2005) showed that positioning patients with ARDS at 40° to 45° of uprightness in dorsal decubitus position improved the P/F ratio in all patients. This improvement was considered significant in 66% of patients. Patients who did not respond to this position had thoracic trauma or lung surgery. In this study, patients were so positioned for 12 hr, during which none had any major hemodynamic problems. Only 5 patients required vascular filling without the use of amines (511 ml). At the beginning of the positioning maneuver, 72.2% of the patients were on norepinephrine (0.44 μg/kg/min) and 22% on dobutamine (10 µg/kg/min). During the 12 hr of the technique, there was no significant change in hemodynamic parameters.

In 2006, Richard et al. (RICHARD; Intensive Care Med; 2006) showed that a pseudo-upright position (head of the bed raised to 45° and foot of the bed lowered to 45°) significantly improved the PaO_2_ (94 ± 33 up to 142 ± 49 mmHg) in some responder patients (11 of 16). The end-expiratory lung volume was also increased in the "pseudo-upright position". The physiological explanation would be alveolar recruitment resulting in a greater lung volume without modification of the thoraco-pulmonary viscoelastic properties or the thoraco-pulmonary specific compliance.

However, this pseudo-verticalization technique has not been studied further in ARDS. Indeed, the use of PP has become routine for managing ARDS in patients. A multicenter study by Guérin et al. (PROSEVA study), showed decreased mortality in > 400 ARDS patients. Daily use of PP for 16 hr reduced mortality by 50% on days 28 and 90 as compared with conventional management (GUERIN; N Engl J Med; 2013).

In 2011, in a prospective randomized cross-over study (ROBAK; Crit Care; 2011), combining prone and upright positions improved oxygenation in ARDS patients. The patient was placed in the prone position with the top of the bed raised and the foot of the bed lowered. The upright position corresponds to an elevation of the top of the bed and a lowering of the leg section, thus resulting in a tilting of the bed in a pro-trendy position. This position improved PP effects in responders. Non-responders had higher P/F ratio than responders at the time of PP [169 (13-257) vs 123 (90-149)]. Responders showed decreased oxygenation when the patient was repositioned in conventional PP. As soon as the patient was repositioned in the upright position, oxygenation again improved. This observation excluded a time-dependent effect on oxygenation. In this study, the measurement of effects on oxygenation was performed only over an 8-hr period.

In 2013, Dellamonica et al. (DELLAMONICA; Intensive Care Med; 2013) showed that ARDS patients responding to the upright position had lower lung compliance than non-responders [30 ml/cmH2O (22-38) vs 42 ml/cmH2O].

In spontaneously breathing patients, Ding et al. (DING, CRIT CARE, 2020) showed that the use of PP in non-intubated patients (2 hr twice a day) with high-flow oxygen therapy support decreased the need for intubation in patients with moderate to severe ARDS.

The prone position is not feasible for all patients with ARDS. The absolute contraindications are pregnancy, major hemodynamic instability, open abdominal surgery, and unstable fractures (GATTINONI; Am J Respir Crit Care Med; 2013).

### COVID-19, ARDS and PP

No studies have been published regarding the value of PP in non-intubated COVID-19 patients (whether classified as having "ARDS" based on their PaO_2_/FiO_2_ ratio assessed on spontaneous breathing [PaO_2_/FiO_2_<300 or <200] or not).

Two clinical observations result from published cohort studies of COVID-19 patients:

1) On admission to the hospital and ICU, chest CT most often shows a major interstitial syndrome with no or little alveolar filling or consolidation (ZHOU, AJR Am J Roentgenol, 2020).

2) Yet, daily observation of intubated COVID-19 patients shows that PP, which is known to result in a good response in terms of oxygenation only when there is alveolar filling of the declivities in the supine position, shows that a large majority of patients are responders.

To explain this "paradoxical" effect, the classic "re-aeration" of the filled or condensed declivities (which allows for readjustment of the ventilation/perfusion ratio towards a better ventilation) due to PP is not sufficient. The PP in this case may have a predominant effect on vascularization: a predominant effect on the "perfusion" part of the ventilation/perfusion ratio, which would lead to a better perfusion of the best ventilated areas and thus a decrease in the shunt effect. However, the best ventilated areas are difficult to localize and are likely to be diffuse.

COVID-19 coronavirus (2019-nCoV) enters the cell by binding the S1 part of its Spike protein to the angiotensin converting enzyme II (ACE2) receptor [ZHOU, NATURE, 2020]. The intensity of viral respiratory infection depends on the degree of host cell maturation and the level of expression of ACE2 and its receptor in cells of the respiratory epithelium and vascular endothelium [IA; J Virol; 2005]. ACE converts angiotensin I to angiotensin II, whereas ACE2 cleaves a different hexapeptide, angiotensin-1Y7 (Ang-1Y7) from angiotensin II. ACE2 regulates the renin-angiotensin system directly by reducing the coupling of angiotensin to the ACE receptor but also by activating a counter-regulatory pathway through the Ang 1-7/Mas receptor pathway [KHAN; Crit Care; 2017/JUILLERAT-JEANNERET; J Med Chem; 2020]. ACE inhibition (by classical ACE inhibitors) seems to have a protective effect in ARDS, without knowing whether it is the reduced ACE activity level or on the contrary the ACE/ACE2 balance more favorable to ACE2 that explains the protective power [LI; Schock; 2015.]

Angiotensin II is a potent vasoconstrictor, active on vascular smooth muscle cells. Ang(1-7) produced by ACE2 from angiotensin II induces arachidonic acid production and nitric oxide synthase activation in all tissues but predominantly in the brain [JUILLERAT-JEANNERET; J Med Chem; 2020.]. Thus, the ACE2 pathway has overall tissue-protective effects, notably tested in ARDS [KHAN; Crit Care; 2017], owing to its various anti-proliferative, anti-apoptotic, anti-fibrotic, and microvascular vasodilatation effects.

Therefore, the hypoxemia of COVID-19 may at least in part be related to a disruption of the ACE2 pathway at the pulmonary microvascular level owing to the congestion of its membrane receptors by viral proteins. In parallel, the same hypotheses, this time with the prospect of a pharmacological intervention on this pathway, have been put forward recently [Vaduganathan; N Engl J Med; 2020].

Of course, this scenario does not provide a clear explanation for the finding of a significant effect of PP on oxygenation in COVID-19 patients, but the changes in blood flow at the thoraco-pulmonary level brought about by the PP maneuver may be able to reduce, for an undetermined time, the microvascular detrimental effects of the partial inhibition of the ACE2 pathway. An effect, even if limited in time, would have a favorable effect on oxygenation, which could benefit the patient.

## Description of the considered strategy

We hypothesize that the use of prone position in spontaneously breathing COVID-19 patients under oxygen therapy would reduce the rate of intubation or non-invasive ventilation at 2 pressure levels.

# Objectives of the study

## Primary objective

To demonstrate that PP in spontaneously breathing patients decreases the risk of acquiring the following events, which can be seen as a composite endpoint:

- Endotracheal intubation

- Or non-invasive ventilation at two pressure levels

- Or death

However, we plan to include only patients without an order to not intubate so that if an imminent life-threatening respiratory occurs, intubation will be performed. Thus, only sudden unexpected death not likely to be related to respiratory function could occur and be counted in this composite criterion without endotracheal intubation or non-invasive ventilation.

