## Non-inclusion criteria

Patients on oxygen therapy or continuous positive airway pressure or non-invasive ventilation at home

Patients with COPD (Gold stage 3 or 4)

Patients with known chronic diffuse interstitial lung disease

Patients with a chronic neuromuscular pathology

Contraindication to prone position (recent thoracic trauma, pneumothorax, unstable spine or pelvis fractures etc.)

Deep vein thrombosis or pulmonary embolism with curative anticoagulation for < 48 hr

Hemodynamic instability (mean arterial pressure < 65 mm Hg) persisting for > 1 hr

Respiratory rate > 40 cycles/min

Excessive use of accessory respiratory muscles (as determined by the clinician)

Indication for curative non-invasive ventilation (acute pulmonary edema or acute hypercapnic respiratory failure)

Intestinal occlusive syndrome

Patients unable to protect upper airway

Patients discharged from intensive care after having treatment with invasive or non-invasive ventilation for COVID-19

Inability to understand French or to follow instructions to perform awake PP

Patients not affiliated or excluded from the French social security system or under law protection (namely minors, pregnant or breastfeeding women, persons deprived of their liberty by court or administrative decision)

Do not intubate order

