## Emergency treatment

If PP induces a major decrease in SpO2 for more than 5 min or a non-resolving tachycardia despite a return to the classical sitting position or an adaptation of the oxygenation or non-invasive ventilation parameters by the clinician in charge of the patient, we will record this event as a non-serious AE if the supine position improves this parameter. However, if, despite the supine positioning, the patient does not show improvement of respiratory parameters, we will record a serious AE related to the PP.

If the respiratory signs deteriorate significantly, the use of non-invasive ventilation with 2 pressure levels or intubation will be possible if the clinician in charge of the patient considers it necessary. If intubation is considered unreasonable because of the evolution of the disease and vital parameters, although the patient would have initially received treatment in the ICU, appropriate care will be implemented for comfort in accordance with the practices of each department.

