## Statistical methods

A detailed analysis plan will be developed prior to the start of the study. The plan will be modified, if necessary, before the statistician is unblinded.

Oatient characteristics will be described by randomization group as number and percentages for categorical variables and mean (standard deviation) or median (25th and 75th percentile) for continuous variables, depending on their distribution.

The main analysis will be conducted on an intention-to-treat basis. However, data for patients withdrawing their consent during the study, in accordance with French law, will not be analyzed.

The primary endpoint (percentage of patients requiring intubation or non-invasive ventilation at 2 pressure levels, or who died within 28 days of inclusion) will be compared between the 2 groups (PP and usual care) by a Mantel-Haenszel 2-test stratified on the stratification variables #2 and #3 (SpO2 and BMI). The effect of the intervention will be expressed in terms of absolute risk difference and its 95% confidence interval (CI). The result of this analysis will be confirmed by a mixed-effect logistic regression analysis, with the recruiting center as the random effect and the study intervention and the stratification variables 2 and 3 as fixed effect variables. Interaction terms between the stratification variables and the intervention will be introduced into the model and retained only if they show a significant effect on the frequency of the outcome. Logistic regression analysis will be used to estimate the odds ratio and its 95% CI.

The binary secondary endpoints (intubation rate, rate of non-invasive ventilation at 2 pressure levels, rate of transfer to ICU, mortality) will be compared between the groups using the same method.

The time to clinical improvement (decrease of 2 points on the WHO scale) will be compared between groups by log rank test and presented as Kaplan-Meier curves. The difference in risk between the groups will be expressed as a hazard ratio (HR) and its 95% CI. This analysis will be secondarily adjusted for stratification variables, and possibly other covariables that would be misbalanced between groups, using a Cox proportional model provided the proportional assumption is verified.

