## Management of missing, unused or invalid data

In this trial and considering that the protocol will be respected, no missing data are expected for the intervention, stratification and endpoint variables. Vital status at 28 days for patients discharged before D28 will be collected by telephone call by a member of the research team (as a precaution, the town of birth of each included patient will be noted at inclusion in order to collect vital status from city halls if necessary). Patients who withdraw their consent will be excluded from the analysis as required by French law, and it is not planned to replace them by imputation for the main analysis. However, the number of patients withdrawing their consent will be analyzed to assess whether it does not reveal an imbalance between the 2 randomization groups, which could be related to a less tolerance of either arm.

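### The protocol rules out respiratory deaths without intubation or NIV but elsewhere allows them, and the stand-alone intubation and NIV rates count such deaths as non-events

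*Protocol*

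**What the plan says.** Under Primary objective, the protocol justifies counting death in the composite as follows: "we plan to include only patients without an order to not intubate so that if an imminent life-threatening respiratory occurs, intubation will be performed". It concludes that "only sudden unexpected death not likely to be related to respiratory function could occur and be counted in this composite criterion without endotracheal intubation" or NIV.

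The premise is an entry criterion. Section 4.2 (Non-inclusion criteria) lists "Do not intubate order", which governs who is randomised and not what is decided afterwards.

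Section 6.3 covers what happens later. When respiratory signs deteriorate significantly, two-level NIV or "intubation will be possible if the clinician in charge of the patient considers it necessary". It then continues: "If intubation is considered unreasonable because of the evolution of the disease and vital parameters", with the consequence that "appropriate care will be implemented for comfort in accordance with the practices of each department".

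The Secondary endpoints include the intubation rate and the NIV rate, each at 28 days and without death as part of the event, and a combined version over the whole hospital stay. Section 8.1 (Statistical methods) says that the binary secondary endpoints "will be compared between the groups using the same method" as the primary: a stratified Mantel-Haenszel test with a risk difference. The main analysis is by intention to treat. Mortality is a separate secondary endpoint.

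**The concern.** The statement about deaths is the protocol's only reasoning on patients who die without ventilatory support, and section 6.3 describes the very case it excludes. If such deaths occur, the composite handles them correctly but the component rates do not. A patient who deteriorates, is not intubated and dies stays in the denominator as not intubated and, if never given NIV, as not given NIV either.

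The synopsis words its secondary objectives as demonstrating that prone positioning reduces intubation and reduces NIV. The trial is open label (Blinding methods), so those who decide on intubation know the allocation, and comfort care follows each department's practice. A lower intubation rate could then partly reflect more deaths without intubation, and a secondary conclusion drawn from that rate alone could mislead.

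**Working it through.** **1. The passages side by side**

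| Step | Primary objective | Section 6.3 |
|---|---|---|
| Life-threatening respiratory event after inclusion | Intubation will be carried out | NIV or intubation possible, at the clinician's discretion |
| Intubation judged unreasonable | Not foreseen | Comfort care by local practice |
| Death without intubation or NIV | Only sudden and unlikely to be respiratory | A respiratory death without intubation is possible, and without NIV if none was given |

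As written, these cannot both hold.

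**2. The plan's own figure (section 8.2)**

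Inputs: two-sided alpha 5%, power 80%, 1:1 allocation, composite rates 4% vs 14% or 10% vs 24%, loss below 2%.

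n per arm = [1.96·√(2·p̄·(1−p̄)) + 0.8416·√(p1(1−p1)+p2(1−p2))]² / (p1−p2)²

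- 4% vs 14%: (0.793 + 0.335)² / 0.01 gives 128 per arm, 256 in total, and 256/0.98 gives 262.
- 10% vs 24%: (1.041 + 0.439)² / 0.0196 gives 112 per arm, 224 in total, and 224/0.98 gives 229.
- With 134 per arm the power is 82.0% and 86.7%.

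The 268 is therefore supported. It is also untouched by this point, because the composite counts every death.

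**3. How a component rate behaves**

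In one arm, let I be the proportion intubated and D the proportion who die without intubation. Then intubation or death = I + D, and between arms

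difference in I = difference in (I + D) − difference in D.

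The intubation contrast departs from the intubation-or-death contrast by exactly the between-arm difference in D. One patient in 134 is 1/134 = 0.75 percentage points.

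**4. Illustrative size**

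The documents give no number of unsupported deaths, so a share s of composite failures is assumed to be deaths with neither intubation nor NIV. The endpoint here is intubation or NIV with deaths left out, so its rate is p·(1−s).

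*Same share in both arms (attenuation):*

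| Composite rates | s | Observed difference | Power, 134 per arm |
|---|---|---|---|
| 24% vs 10% | 0 | 14.0 points | 86.7% |
| | 10% | 12.6 | 82.1% |
| | 30% | 9.8 | 70.0% |
| 14% vs 4% | 0 | 10.0 | 82.0% |
| | 10% | 9.0 | 77.3% |
| | 30% | 7.0 | 65.6% |

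*No true effect, share different between arms (bias):* false difference = p·(s in arm A − s in arm B).

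- p = 14%: 0.14 × 0.10 = 1.4 points; 0.14 × 0.30 = 4.2 points.
- p = 24%: 0.24 × 0.10 = 2.4 points; 0.24 × 0.30 = 7.2 points.
- In patients: 134 × 0.014 = 1.9, up to 134 × 0.072 = 9.6.

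An equal share shrinks a true difference. Only an unequal share creates a false one.

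**The case against.** The strongest counter-argument is that little is hidden. The primary endpoint counts all deaths, mortality is prespecified and compared by the same method, and reporting components beside a composite is normal practice. An imbalance in unsupported deaths would show in the mortality line. The unseen analysis plan that section 8.1 announces might also treat death as a competing event. This limits the damage to the interpretation of two secondary rates and their whole-stay version. It does not remove the contradiction, which lies in the protocol itself, and section 8.1 already fixes a method with no rule for death.

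Section 6.3 can also be read narrowly. Its comfort-care sentence concerns intubation only and mentions patients who would initially have been treated in the ICU. Some of them may have had NIV first and would count as NIV events. That stands: section 6.3 shows that such deaths may occur, not that they will.

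Four stronger readings are tempting, and the documents do not support them:

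- *Respiratory deaths at home.* Section 8.5 says "Vital status at 28 days for patients discharged before D28 will be collected by telephone call". It names vital status only, so it shows that deaths after discharge are counted, not that they are respiratory.
- *A death count from the background mortality of 5% to 15%.* At 10%, 268 patients would give about 27 deaths. That exceeds all composite events in the protocol's own 4% vs 14% scenario (134 × 0.04 + 134 × 0.14 = 24.1). The background figure covers hospitalised patients in general, not a population without do-not-intubate orders.
- *A false demonstration of benefit.* Even assumed counts of 14 vs 20 intubated of 134 (10.4% vs 14.9%) give z = 0.0448/0.0407 = 1.10 and p of about 0.27.
- *Direct intubation as a flaw in the NIV rate.* It does lower that rate, as with any component, but the intubation rate and the composite both capture those patients.

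**Conclusion.** The point holds in limited form. The Primary objective text and section 6.3 conflict and must be reconciled; this review does not say which clinical rule is right. The primary analysis and the sample size of 268 are unaffected. The 28-day intubation and NIV rates count unsupported deaths as non-events, which would flatter an arm with more of them.

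The size is unknown. Under the assumed imbalance of 10 to 30 percentage points in the share of unsupported deaths, with equal true failure of 14% or 24%, the false benefit is 1.4 to 7.2 points (about 2 to 10 patients per arm), against planned composite effects of 10 to 14 points. Without an imbalance there is attenuation and no false benefit. Open-label decisions and department-specific practice make an imbalance possible; nothing in the documents shows that it will arise.

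**What to change.** - Reconcile the Primary objective text with section 6.3, and remove or qualify the sentence on deaths so that it claims no more than the reconciled text guarantees.
- In section 8.1, keep the prespecified intubation and NIV rates. Add intubation or death by day 28, with the same stratified test and risk difference. State that any claim of reduced intubation rests on both results read together with mortality.
- Tabulate by arm the deaths without intubation, the deaths without NIV, the deaths without either, and any treatment-limitation decision after randomisation found in the hospital record.

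The cost is a wording change and one further secondary analysis. That analysis uses intubation and death data already needed for the primary endpoint; the treatment-limitation decisions must be extracted from the hospital record. The drawback is that the added endpoint overlaps heavily with the primary composite, differing only in survivors who had NIV without intubation, so the separate component rates must still be shown.

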## Secondary objectives

The duration (in days) to improve (score decrease) the clinical WHO ordinal scale score from randomization to 28 days between the 2 groups (PP and usual care)

The rate of endotracheal intubation (%) for invasive mechanical ventilation at 28 days between the 2 groups

The rate of non-invasive ventilation at 2 pressure levels at 28 days between the 2 groups

The time on oxygen therapy from inclusion to day 28 between the 2 groups

The hospital length of stay between the 2 groups

The mortality at 28 days and during the hospital stay between the 2 groups

The rate of transfer to an ICU at 28 days

The rate of use of non-invasive ventilation at 2 pressure levels and intubation over the entire hospital stay

## Primary endpoint

The rate of treatment failure defined as a composite endpoint comprising intubation and/or non-invasive ventilation at 2 pressure levels and/or death, in each group (PP and usual care).

## Secondary endpoints

The duration (in days) to improve the clinical WHO ordinal scale from randomization to 28 days between the 2 groups (PP and usual care). This scale is recommended by the WHO (<http://www.who.int/blueprint/priority-diseases/key-action/novel-coronavirus/en/>) and was used in clinical trial of COVID-19 (CAO; N Engl J Med; 2020). This scale is relevant but it could be difficult to use for overloaded wards during an epidemic to exhaustively survey all points. Moreover, because the unit of time is the day, the score is imprecise (e.g., for reasons of feasibility, it is not possible to envisage twice-daily surveying). For this reason, the scientific committee chose not to use this endpoint as primary endpoint.

The rate of endotracheal intubation (%) for invasive mechanical ventilation at 28 days between the 2 groups

The rate of non-invasive ventilation at two pressure levels at 28 days between the 2 groups

The time passed on oxygen therapy from inclusion to day 28 between the 2 groups

The hospital length of stay between the 2 groups

The mortality at 28 days and during the hospital stay between the 2 groups

The rate of transfer to ICU at 28 days

The rate of use of non-invasive ventilation at 2 levels pressure and intubation over the entire hospital stay.

